## Abstract

**Background:**

Functional decline (FD) is a largely preventable feature of aging, characterized as gradual erosion of functional autonomy. This reduces an older person’s capacity for safe, independent community living. The healthcare needs of an unprecedented aging population places pressure on health systems to develop innovative approaches to ensuring older people live healthy and independent lives for as long as possible.

TRIIFL aims to demonstrate that:

1. Incipient FD in older people can be identified using a simple telephone-screening process within four weeks of discharge from an emergency department presentation for a minor health event; and

2. Early engagement into a person-centered individualized intervention arrests or reduces the rate of FD over the next 12 months.

**Methods/Design:**

A randomized controlled trial (RCT) nested within a 13-month longitudinal cohort study. The RCT (conducted over 12 months) tests the effectiveness of a novel, early, home-based, personalized program (compared with no intervention) in arresting or slowing FD.

TRIIFL focuses on older adults living independently in the community, who have not yet had a serious health event, yet are potentially on the cusp of FD. Participants in the longitudinal cohort study will be recruited as they present to one large tertiary hospital Emergency Department, providing they are not subsequently admitted to a ward. Sample size calculations indicate that 570 participants need to be recruited into the longitudinal study, with 100 participants randomized into the trial arms.

Measures from all subjects will be taken face-to-face at baseline (recruitment), then subsequently by telephone at one, four, seven and thirteen months later. Measures include functional abilities, quality of life, recent falls, mobility dependence, community supports and health service usage. Specific to the nested RCT, the quality of life tool (SF12) applied at one month, will identify individuals with low mental component quality of life scores, who will be invited to enter the RCT.

Assessors will be blinded to RCT arm allocation, and subjects in the RCT will be blinded to the intervention being received by other subjects.

**Trials Registration:**

Australian & New Zealand Clinical Trials Registry: ACTRN12613000234718

## Study aim

1. To determine whether an individualized early intervention for community-dwelling older people with poor mental component quality of life scores measured one month after discharge directly from a hospital emergency department (ED), reduces their likelihood and/or rate, of functional decline (FD) over the next twelve months.

2. To demonstrate that:

a. Incipient FD in an older person can be identified within four weeks of discharge from an ED presentation for a minor health event, using lower than median mental component quality of life scores; and

a. Engaging these older people early, into a person-centered home-based intervention, arrests or reduces the rate of FD over the next 12 months.

## Background

The immediate future presents Australian and global health policy challenges in how to meet the health needs of an aging population of unprecedented size [1]. Prevention rather than treatment is a critical requirement. The potential for FD with increasing age is outlined by Edwards *et al*. [2], who illustrated that with age, an increasing number of people are classified as below the ‘disability threshold’, putting them at significant risk of preventable health crises such as falls, malnutrition and/or infections. In 1950, less than 1% of the global population was over 80 years old, but by 2050 this proportion is expected to be 4%. The greatest increase will be in Organisation for Economic Co-operation and Development (OECD) countries where the portion of the population over 80 years old is expected to increase from an average 4% to 9.4% [1]. In Australia the number of people 85 years + will quadruple from 0.4 million in 2010 to 1.8 million in 2050 [3]. In 2009 to 2010, Australian government spending on aged care was around $11 billion; two thirds of that was in residential aged care [4]. Institutional care use and acute care support needs of older people will place commensurate pressure on health systems to develop innovative new approaches to ensuring older people live healthy and independent lives for as long as possible [1].

### Functional decline

FD is a largely preventable feature of aging, characterized as gradual erosion of functional autonomy, which reduces an older person’s capacity to live safely and independently in the community [5-7]. FD encompasses both physical and cognitive function. It is commonly accepted that FD precedes frailty [8]; however, there is no standard approach for defining or measuring either state [8,9]. Reduced functional ability is associated with increased mortality and morbidity rates, increased use of health services in all sectors and greater rates of institutionalization [7,10,11].

There are a number of Australian federal and state health and aged care service initiatives to support ‘aging in place’ , aiming to optimize older people’s health, dignity, confidence, self-esteem and independence. However, these initiatives largely center on older people ‘known to the system’ [12]. Many older people on the cusp of FD do not come to the attention of healthcare providers until they are in health and/or social crisis [2], and by then it may be too late for effective intervention. Even individuals who are already receiving community services at home, such as Government-funded community care packages, may not be receiving the care required to prevent FD [13].

The current lack of focus on early FD results from: a) the lack of comprehensive primary health capture points where older people are routinely screened for functional and cognitive capacity; b) no comprehensive, timely or sensitive screening tool to identify older people with incipient FD; and c) no early-intervention program which has been shown to have long term effectiveness to prevent, or slow, the rate of, FD.

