### Baseline screening

We will collect data in the ED (baseline) on consenting, eligible participants from

•the electronic hospital admissions system - age, gender, residential details, differential diagnosis; and

•a test battery as successfully piloted in our 2011 study [37]. This captures the highest level of schooling, primary language, ED presentations and hospitalizations in the past six months, falls in the past twelve months using the Falls Risk in Older People - Community (FROP_COM) instrument [39], living arrangements, requiring a carer, receiving community services, type and use of gait aid, iADLs[19] and cognition with the Mini Mental State Examination (MMSE) [40].

Based on data from our pilot study, we will additionally apply the Katz *et al*. [18] 20 basic ADL instrument and two quality of life measures – the SF12 [41,42] and the Australian Quality of Life (AQoL 4D) [43]. By collecting both basic and iADL scores, we can provide comprehensive ADL information about the target population to compare with international data. The SF12 provides the opportunity for international population-based comparisons of quality of life [41,42] with our sample of older ED presenters. The AQoL, which has not previously been used for older people discharged from ED, provides an Australian perspective on health-related multi-attribute utility quality of life [43], and allows production of health cost effectiveness data (quality-adjusted life years (QALYs)), and estimation of burden of disease.

This total test battery takes an average of 5.5 minutes to administer. All but two questions are delivered verbally by the recruiting researcher, who records the answers. The older person only has to write responses to two MMSE questions.

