### Outcome measures

At one, four, seven and thirteen months after recruitment, all participants will be contacted by telephone and consent sought for interview. Socio-demographic information will be confirmed, and all outcome instruments and mutable independent variables will be recorded (Table 1). Semi-structured questions will be asked about how participants are managing, their concerns and reasons for subsequent hospitalizations and ED presentations. At the four, seven and thirteen month data collection points (after nested RCT commencement), assessors will be blinded to group allocation.

**Table 1 T1:** Timeframes of outcome measurements

**Measures**	**Baseline**	**1 month**	**4 months**	**7 months**	**13 months**
ADLs	√	√	√	√	√
iADLs	√	√	√	√	√
SF12	√	√	√	√	√
AQoL_4D	√	√	√	√	√
Falls	√ (last 12 months)	√ (last month)	√ (last 3 months)	√ (last 3 months)	√ (last 6 months)
Hospitalizations	√ (last 6 months)	√ (last month)	√ (last 3 months)	√ (last 3 months)	√ (last 6 months)
Gait aid (type)	√	√	√	√	√
Living arrangements	√	√	√	√	√
Carer engagement	√	√	√	√	√
Organized (formal) community services	√	√	√	√	√
GP visits	√	√	√	√	√
Informal community supports	√	√	√	√	√
Satisfaction with community supports	√	√	√	√	√

ADLs, activities of daily living; AQoL_4D, Australian Quality of Life; GP, general practitioner; iADLs, instrumental activities of daily living; SF12, Short Form-12 Health Survey; √ indicates an occasion of data collection.

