### Additional data and calculations

From baseline information on age, iADLs and MMSE scores, a HARP score will be determined [17,36]. HARP, while sensitive to approximately 63% only, is useful for comparing FD risk in our sample with other Australian and international studies. Validation details of the index ED presentation will be undertaken via patient record audit to verify age, presenting diagnosis, previous hospitalizations and ED discharge plans (if any).

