### Study 1 analysis

FD will be assessed as change from baseline at each time point as:

•One or more falls increase from the baseline rate

•More than one event of hospitalization, or ED presentation, from the baseline rate

•Decrease of one point in any item of the ADL instrument [18], or

•Decrease of 2+ points from baseline total iADL score [19], or any decrease in baseline score in the domains of home activities, doing laundry, shopping and getting places (we previously reported these domains as critical to functional independence) [37]

•Scores decreasing from above median at baseline in either physical or mental domain, to below median in the SF12 [41,42]

•Any decrease in AQoL_4D (in the manner recently described for chronic obstructive pulmonary disease (COPD))[44]

•Change to a more assistive gait aid (for example, a one point stick to a four-pronged stick)

•Change in living arrangements to more supported care

•Increased carer involvement

•Greater type and frequency of use of formal community services or informal supports

•More frequent GP attendances.

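### Functional decline is described as physical and cognitive, but cognition is tested directly only at baseline, so a conclusion that decline as a whole is absent or arrested goes beyond what is measured

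*Protocol article*

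**What the plan says.** In the Background, under Functional decline, the article states that "FD encompasses both physical and cognitive function".

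Under Baseline screening, the battery given in the emergency department includes "cognition with the Mini Mental State Examination (MMSE) [40". The rest of the battery is verbal: "The older person only has to write responses to two MMSE questions".

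Under Additional data and calculations, the MMSE has one stated use: "From baseline information on age, iADLs and MMSE scores, a HARP score will be determined".

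Under Outcome measures, follow-up is by telephone: "At one, four, seven and thirteen months after recruitment, all participants will be contacted by telephone". That section refers the reader to Table 1 for what is collected. Table 1 has no MMSE row and no other cognitive test.

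Under Study 1 analysis, the operational definition opens with "FD will be assessed as change from baseline at each time point as" and lists eleven criteria. One of them is "Decrease of 2+ points from baseline total iADL score [19", with an alternative trigger of any loss in four named household and mobility domains. None of the eleven is a change in a cognitive score.

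The Study aim section speaks of preventing or slowing FD over twelve months and does not limit the term. In the Hypotheses section, Hypothesis 3 expects no FD in the intervention cohort and likens this to the findings in the observed cohort. Hypotheses 1 and 2 are tied to the study's measures.

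**The concern.** The concept has two stated components, and one of them is not tested directly after baseline. A participant whose cognition falls over the 13 months, with no reported change in any listed item, is counted as having no FD. Statements that decline is absent or has been arrested are the ones most exposed to a component nobody observed.

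Two features add to this. First, the follow-up data come from telephone interviews that ask for recall of falls and hospitalizations over up to six months. Cognitive loss could weaken those reports, and no direct test would show it. Second, the article itself warns, under How is FD detected?, that assessment in the emergency department may be unreliable because people there can be unwell or disoriented. The single cognitive measurement is taken in that setting.

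At stake is the scope of the trial's headline claim. A reader who takes the background definition at face value would credit the intervention with protecting cognition when the trial has no direct evidence on that.

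**Working it through.** No formula applies and the plan gives no figure to reproduce. The check is a count of direct cognitive measurement at each step from concept to conclusion.

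1. **Concept (Functional decline).** Two components are named: physical and cognitive.
2. **Contacts (Table 1).** Baseline and months 1, 4, 7 and 13 make 5. Cognition is tested directly at baseline only: 1/5 = 20%. Allocation takes place at month 1, so the contacts after randomization are months 4, 7 and 13: 0 of 3.
3. **Follow-up measures (Table 1).** There are 13 rows: ADLs, iADLs, SF12, AQoL_4D, falls, hospitalizations, gait aid, living arrangements, carer engagement, formal services, GP visits, informal supports, and satisfaction with supports. Direct cognitive tests: 0 of 13.
4. **FD criteria (Study 1 analysis).** There are 11 bullets: falls, hospital or emergency use, ADL, iADL, SF12, AQoL_4D, gait aid, living arrangements, carer involvement, services and supports, and GP attendance. Direct cognitive criteria: 0 of 11.
5. **Indirect capture.** Loss of a complex daily task, more carer involvement or a move to more supported living can each follow from cognitive decline. Each can equally follow from physical decline, so these criteria are sensitive to some cognitive loss but not specific to it. The SF12 mental component is a quality-of-life score, not a test of cognition.
6. **Conclusion (Study aim; Hypotheses).** The aims use FD without qualification. Hypothesis 1 is restricted to the FD measures and Hypothesis 2 to the outcome measures. Hypothesis 3 is worded as no FD, with a comparison to the observed cohort.

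Taking steps 1 to 5 with step 6, the aims and Hypothesis 3 claim more than the measurements support; Hypotheses 1 and 2 largely do not.

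The wording of the remedy also depends on the count in step 4. Only 2 of the 11 criteria are ADL or iADL, so 11 − 2 = 9 are something else. Restating the outcome as decline in daily activities alone would misdescribe those nine.

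**The case against.** The strongest defence is that the sentence on cognition is background. The same section characterizes FD as loss of functional autonomy and says that no standard definition or measure exists. A later section notes that FD is usually assessed through ADLs and iADLs. Study 1 analysis then sets an explicit operational definition, and two of the hypotheses are tied to the measures. Measuring autonomy through function is a legitimate choice, and people with diagnosed dementia are excluded. All of this stands, and it is why the point concerns the reach of the conclusion and not the validity of the outcomes. It does not remove the mismatch: the aims and Hypothesis 3 carry no such limit, and excluding diagnosed dementia at entry does not rule out cognitive decline during 13 months.

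Several stronger readings are tempting, and the document does not support them:

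- *No outcome can detect cognitive decline.* A count of zero dedicated tests is not a detection rate of zero. The iADL, carer and living-arrangement criteria may register it indirectly.
- *The MMSE was dropped because it needs written answers.* Only two questions do, and the article gives no reason for leaving it out of follow-up.
- *The follow-up schedule contradicts itself.* The phrase "all outcome instruments and mutable independent variables will be recorded (Table 1" might suggest that cognition should have been included, but the article never classes the MMSE as an outcome or as a mutable variable.
- *Selecting on a low SF12 mental component score aggravates the gap.* That score measures mental quality of life, so it gives no ground for inferring poor cognition.
- *The comparison of arms is biased.* The omission is the same in both arms, and nothing here shows bias on the listed measures.

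**Conclusion.** The point holds as a gap between concept and measurement. Cognitive change is directly assessed at 0 of 3 contacts after randomization and in 0 of 11 FD criteria. A conclusion that FD as a whole is absent or arrested therefore exceeds the evidence the trial will collect. Its effect on any estimate cannot be sized from the document, because no rate of cognitive decline is given, nor any figure for how often such decline would surface through the indirect items.

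The verdict rests on reading Table 1 and the criteria list as complete, which is how they are presented. It also takes the background description as the construct to which the aims refer. If the sponsor regards the Study 1 analysis list as the whole definition of FD, saying so in the aims would settle most of the point. A later analysis plan could not settle it by analysis alone, since cognitive change that was not collected cannot be analysed.

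**What to change.** 1. **Narrow the conclusion.** In Study aim, Study 1 analysis and Hypotheses (Hypothesis 3 above all), define FD for inference as decline in the functional, quality-of-life, falls, support and service-use outcomes listed under Study 1 analysis. Do not reduce it to ADL and iADL. Add one sentence saying that cognitive change is not directly assessed after baseline.
2. **Use the baseline MMSE.** Enter it as a covariate in the models described under Analysis of data from Studies 1 and 2. It is already collected, and the protocol already treats it as part of a risk score for FD. This adjusts for differences in starting cognition; it does not replace the missing follow-up measurement.
3. **Optional, if the wider claim is to be kept.** Add orally answerable cognitive items to every telephone call from month 1, and score change only on the items common to all calls. The month 1 call, made before allocation, then gives a reference value by the same mode and outside the emergency department.

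The first two changes cost some wording and one model term; the real price is a narrower claim. The third adds interview time, put here at a few minutes per call as an assumption, since the document gives no figure for it.

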### The importance of detecting FD after an ED presentation

Evaluation of recent changes to the way that general medical practitioner (GP) services are being provided in Australia (for example, by large corporate health services or in multidisciplinary community clinics) suggest that many older people now do not have regular contact with the same GP [14,15]. This potentially attenuates opportunities for regular monitoring of older persons’ functional abilities or flagging the need for intervention before FD becomes critical. In Australia, decreasing opportunities and incentives to maintain contact with a regular GP may be related to the increasing number of frail, community-dwelling older people who appear to rely on hospital EDs for crisis health management [16]. These individuals often do not require admission to hospital for acute care. Rather, their needs are more for health assessment and short-term management strategies and for linkages to appropriate community supports to assist them to maintain safe community independence in the longer term. Thus, whether or not it is the right place, ED attendance without a subsequent hospital admission, is an increasingly important service-contact point related to incipient FD.

### How is FD detected?

FD generally occurs subtly and can remain undetected until an unexpected and often catastrophic event occurs [6]. This can be a fall or unexplained ill health which requires hospitalization. This event, if followed by a comprehensive assessment, can expose the magnitude of an individual’s loss of capacity to function safely and independently [6,7,17].

There are a variety of ways of assessing FD; however, it is most commonly assessed as the capacity to complete basic and instrumental activities of daily living (ADLs and iADLs). Basic ADLs are everyday tasks (bathing, dressing, feeding, continence, transferring, toileting) [18], while iADLs are higher level activities (shopping, driving, banking and so on) [19,20]. Inability to manage ADLs safely and independently may only be temporary, if related to illness. This will usually respond well to recovery time and short-term targeted intervention. FD, however, may be irreversible if identified too late for effective community-based interventions. Individuals who have passed the critical threshold of FD may not be able to live safely at home despite intensive and long-term supports and, thus, may require permanent residential care. Irrespective of the point at which FD is assessed on its trajectory, there is no agreement on the best measures to detect FD nor the point of critical deterioration [21].

Detecting FD early and putting supports in place, as directed by the older person, to redress specific and individual areas of decline has been proposed as a way of maintaining older people’s community independence for a longer time [17,22-25]. Comprehensive frailty indices with multiple screening items have also been proposed from population research, mainly conducted in the UK and Canada [6,21,26,27]. However, there are few opportunities in Australia comprehensively to capture this amount of information from community-dwelling older people who are not in health crisis and who may not routinely come to the attention of the healthcare system. FD screening tools reported in the Australian literature are implemented at ‘point-in-time’, commonly during a health crisis at an ED presentation or hospitalization [28]. In these environments, assessment of FD may be inappropriate, when older people are unwell, disoriented, frightened and/or in unfamiliar environments. This raises issues of validity of assessment and/or reliability of responses.

### Pilot work underpinning this protocol

The TRIIFL study builds on 15 years of research into improving the quality of discharge planning for older people, to ensure that older people were transferred safely from ill health in a hospital bed to health at home [25,28-36]. Our work has highlighted common barriers of lack of ownership and collective responsibility for the problem, lack of time, poor communication and resources, and hospital/community ‘turf wars’. Sadly there have been no real changes in discharge planning standards or outcomes in Australia over this time.

We recently published findings from an innovative longitudinal pilot study we conducted in 2011, into prediction and downstream assessment of FD in older people presenting to, and being discharged from, a large South Australian tertiary hospital ED [37]. This study used a comprehensive data collection process to recruit individuals who were not admitted to a hospital ward, that is, they were discharged directly from ED usually within four to eight hours of presentation. This work clearly showed that ED was the choice for 30 to 60 older people/day, who were eligible for our study and did not have their own GP. In our pilot study, we followed up subjects at one week and one and three months later to follow the course of FD. Estimated likelihood of FD at discharge was made with a comprehensive purpose-built assessment tool, as well as the Hospitals Admission Risk Profile (HARP) instrument [36]. We reported that overall, the likelihood of FD at discharge approximated 50%, significantly more than the 30% predicted in the Australian Discharge of Elderly from the Emergency Department (DEED) study [38]. Of note in the 2011 pilot study was the percentage of ‘younger’ old patients (65 to 75 years old) who had significant risk of FD, despite attracting no age weighting from the HARP instrument.

The TRIIFL protocol is based on a novel finding from this pilot research, that subjects with lower than median mental component scores (MCS) on the Short Form-12 Health Survey (SF12) quality of life instrument [39,40], administered one month post-discharge from the ED, were significantly more likely to demonstrate FD two months later (identified as significant reduction in iADL scores, increased falls and hospitalizations), compared with individuals with above-median MCS scores at the same time point. We propose that if early intervention was offered to individuals with low mental health quality of life scores at this point in time, progression of FD could be altered.

